## Abstract

**Background:**

The majority of nursing home residents with dementia experience behavioural and psychological symptoms like apathy, agitation, and anxiety. According to analyses of prescription prevalence in Germany, antipsychotic drugs are regularly prescribed as first-line treatment of neuropsychiatric symptoms in persons with dementia, although guidelines clearly prioritise non-pharmacological interventions. Frequently, antipsychotic drugs are prescribed for inappropriate reasons and for too long without regular reviewing. The use of antipsychotics is associated with adverse events like increased risk of falling, stroke, and mortality. The aim of the study is to investigate whether a person-centred care approach, successfully evaluated in nursing homes in the United Kingdom, can be implemented in German nursing homes and, in comparison with a control group, can result in a clinically relevant reduction of the proportion of residents with antipsychotic prescriptions.

**Methods/design:**

The study is a cluster-randomised controlled trial comparing an intervention group (two-day initial training on person-centred care and ongoing training and support programme) with a control group. Both study groups will receive, as optimised usual care, a medication review by an experienced psychiatrist/geriatrician providing feedback to the prescribing physician. Overall, 36 nursing homes in East, North, and West Germany will be randomised. The primary outcome is the proportion of residents receiving at least one antipsychotic prescription (long-term medication) after 12 months of follow-up. Secondary outcomes are residents’ quality of life, agitated behaviour, as well as safety parameters like falls and fall-related medical attention. A health economic evaluation and a process evaluation will be performed alongside the study.

**Discussion:**

To improve care, a reduction of the current high prescription rate of antipsychotics in nursing homes by the intervention programme is expected.

**Trial registration:**

ClinicalTrials.gov: NCT02295462

**Electronic supplementary material:**

The online version of this article (doi:10.1186/s13012-015-0268-3) contains supplementary material, which is available to authorized users.

## Background

Prescription rates of antipsychotic drugs for residents in German nursing homes are considerably high [1] and have not changed for years [2–5]. Recent data show that antipsychotics are prescribed for almost 30 % of German nursing home residents [1]. Studies indicate that up to two thirds of antipsychotics for residents are prescribed for inappropriate reasons [6]. Furthermore, antipsychotics are often prescribed for too long without carrying out a regular review [7]. Both long-term and short-term use of antipsychotics increase mortality compared to non-users [8–10], with cardiac death and infections being the main causes. All antipsychotics are associated with an increased risk of stroke, and the risk might even be higher in patients/residents receiving atypical antipsychotics compared to those receiving conventional antipsychotics [11]. Adverse effects also include sedation, dizziness and increased risk of falling and fall-related injuries, tremor and rigidity [12–16], worsening of cognitive function [17], and other effects which are most likely to result in reduced quality of life (QoL) and well-being as well as withdrawal from social life and participation.

Antipsychotics are mostly prescribed to control behavioural and psychological symptoms of dementia (BPSD) [1]. BPSD are a meaningful clinical target for interventions since restlessness, agitation, aggression, delusions, apathy, disinhibition, and hallucinations are highly prevalent among residents with dementia [18] and pose a major challenge for nursing home staff, frequently leading to distress in patients and carers [19]. The majority of residents with dementia experience BPSD at some point of the dementia trajectory, even in early stages of dementia [20, 21]. These symptoms are highly consistent over the course of five years with a tendency to increase over time [22]. International and national clinical practice guidelines recommend that psychological and environmental approaches should be the first treatment option of BPSD [23, 24], since non-pharmacological interventions individually tailored to the person with dementia are effective [25]. To meet individual needs of residents and improve their QoL, the person-centred care (PCC) approach seems to be appropriate. One highly recognised concept has been introduced by Kitwood [26, 27]. The components of this concept are to regard personhood in people with dementia as increasingly concealed rather than lost, to acknowledge the personhood of each individual in all aspects of care, to personalise care and environment, to offer shared decision-making, to interpret behaviour from the viewpoint of the person with dementia, and to prioritise the relationship as much as the care tasks [28]. Personalised activities were effective at reducing agitation in care home residents [29, 30]. Drugs should only be used as a last resort and should be discontinued immediately after symptoms vanish or improve over a period of 3 months [31, 32]. Thus, nursing homes are urgently requested to strive for a decrease of antipsychotics prescribed for BPSD in favour of non-pharmacological treatment [1].

Systematic reviews [33, 34] indicate that training and support for care home staff reduce prescription of antipsychotics in residents with dementia and can be viable alternatives for managing BPSD. The most recent and most rigorous trial [35], which is the basis for the present study, demonstrates the strongest effect without adverse events. In addition to a PCC approach, a review of drugs was conducted by an old-age psychiatrist taking part in this study [35]. After 12 months, the proportion of residents receiving antipsychotics in the intervention homes (23.0 %) was significantly lower than in the control homes (42.1 %) with an average reduction in antipsychotic use of 19.1 % (95 % confidence interval 0.5 to 37.7 %) [35].

Summarising, to evaluate the intervention programme by Fossey et al. [35] seems to be the most promising approach, although the programme requires a thorough adaptation to the German long-term care and health system.

## Trial objective

The aim of our study is to investigate whether a PCC approach, successfully evaluated in nursing homes in the United Kingdom [35], can be implemented in German nursing homes and, in comparison with a control group, can result in a clinically relevant reduction of the proportion of residents with antipsychotic prescriptions. Our *primary outcome* is the proportion of residents with at least one antipsychotic prescription (long-term medication) after 12 months of follow-up.

A further aim is to investigate whether QoL will improve or at least be unchanged as shown by Fossey et al. [35]. In accordance with the results of the primary efficacy study and a Cochrane review [33], we assume that the intervention is not only effective but also does not harm the residents, i.e. dementia-related BPSD will not worsen in the intervention group, and prescription rates of other psychotropic medication as well as the application of physical restraints will not increase. Therefore, the following *secondary outcomes* will be evaluated (at 12 months):Presence of agitated behaviour,Residents’ QoL,Median daily dose of antipsychotics in chlorpromazine equivalents,Proportion of residents with dementia with antipsychotic prescription,Proportion of residents without dementia with antipsychotic prescription,Prescription prevalence of other psychotropic drugs (antidepressants, anxiolytic and hypnotic drugs, acetyl-cholinesterase inhibitors),Safety parameters are number of falls, fall-related fractures and sutures, fall-related medical attention as well as the proportion of residents with at least one physical restraint (bilateral bedrails, belts, fixed tables, and other measures limiting free body movement), and the number and types of physical restraints.

Additionally, a health economic evaluation will be conducted alongside the study. A process evaluation will also be performed, aiming to comprehensively analyse the underlying processes as well as the barriers and facilitators of the implementation of this multicomponent intervention, giving special focus to regional differences. The programme will be implemented in nursing homes in East, North, and West Germany in order to evaluate its supra-regional generalisability.

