To determine a cut-off point for the QoL-AD self or proxy assessment tool, the validated *Dementia Screening Scale* (*DSS*) [49] will be used as a cognition test (internal consistency: Cronbach’s alpha = 0.94). For this purpose, nursing staff will have to evaluate different aspects of cognitive function regarding seven items with 3-point Likert scales in the domains “memory” and “orientation” over the last 4 weeks (total score ranges from 0 to 14; higher scores indicate more severe cognitive impairment). As the test will be used to decide if a QoL-AD self-assessment is feasible, we will use a cut-off point of >4 (specificity 88.8 %, sensitivity 84.2 %) [49].

Agitated behaviour as one aspect of BPSD will be assessed with a German version [50] of the *Cohen-Mansfield Agitation Inventory* (*CMAI*) [51–53] (measurement points t_0_ and t_4_). The CMAI is a caregiver rating instrument with good psychometric properties of the original version [52] and will be performed by interviewing the nursing staff. The scale consists of 25 items of agitated behaviours, each rated on a 7-point scale of frequency of occurrence over the last 2 weeks (total score ranges from 25 to 175, higher scores mean higher frequencies of manifestation).

To analyse the proportion of residents receiving an antipsychotic prescription, the median daily dose of antipsychotic drugs in chlorpromazine equivalents, and the prescription prevalence of other psychotropic drugs, the following data will be gathered: (1) prescriptions of antipsychotics (long-term and pro re nata (PRN) medication) from routine documentation at t_1_, t_2_, t_3_, and t_4_ retrospectively for the last 3 months: registered trade name or agent, dose, and prescription period; (2) current prescriptions of other psychotropic drugs (long-term and PRN medication) from routine documentation at the time point of t_1_, t_2_, t_3_, and t_4_: registered trade name or agent, and dose.

Additionally, safety and/or adverse outcome parameters like falls, fall-related fractures and sutures, fall-related medical attention, as well as the number and types of physical restraints [2] will be documented at t_1_, t_2_, t_3_, and t_4_ retrospectively for the last 3 months, using data extracted from routine documentation.

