### Sample size calculation

The primary endpoint of the study is the proportion of residents with at least one antipsychotic prescription after 12 months (t_4_). The following sample size estimation was performed as described in Donner & Klar [57] for the cluster-adjusted *χ*^2^-test. Based on recent prevalence data, we expect a baseline prevalence of antipsychotic prescription of 30 % [2]. Due to the measures of optimised usual care in the control group and based on the study by Fossey et al. [35], we expect the prevalence in the control group to decline slightly to 26 % after 12 months. We expect a relative risk reduction of approximately 50 % regarding antipsychotic prescription in the intervention group.

Assuming a significance level of 5 % (α = 0.05), a two-sided test for proportions, and an intra-class correlation coefficient (ICCC) of 0.05, an average cluster size of 65 nursing home residents, 15 clusters are required per group to detect a 12 % difference in proportions from 26 % of the control group at 12 months with 90 % power (β = 0.10). Presuming that six nursing homes might drop out, 36 clusters with a total of 2340 residents will be needed.

We expect 25 % of residents with early study termination due to death or moving; the other 75 % of residents of the baseline population we expect to be still living in the nursing home and to be available for the 12-month follow-up assessment. As the outcome, the analyses will focus on the group of residents living in the nursing homes after 12 months. Assuming that new residents will all be willing to participate in the study, this will not affect the sample size.

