### Statistical analysis

No interim analysis will be performed. Analysis will be based on the intention-to-treat principle. The analysis will be done at the resident level.

For the primary outcome measure, i.e. the proportion of residents with at least one antipsychotic prescription after 12 months, proportions will be compared between the intervention group and control group, using a two-sided cluster-adjusted *χ*^2^-test at a level of significance of α = 0.05 [57]. Corresponding cluster-adjusted 95 % confidence intervals will be calculated. Furthermore, to investigate the time course of the intervention effect, including all the residents observed after 3, 6, 9, or 12 months, drug prescriptions of antipsychotics per resident after 3, 6, 9, and 12 months will be analysed as a dependent variable in a generalised linear mixed (logistic) model with the intervention as a fixed effect, clusters as a random effect, and using covariance patterns to adjust for repeated measurement. This will be done as a secondary analysis.

For the secondary outcome measures, linear mixed models or generalised linear mixed methods will be used, adjusting for clusters by random effects. Subgroup analyses using linear mixed models will be performed for gender and cognitive status. The analysis of all secondary outcomes is interpreted exploratively and not confirmatively.

A detailed description of the statistical analysis can be found in Additional file 2.

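### The primary outcome is limited to long-term antipsychotics, the protocol does not keep to that limit, and no outcome is stated to pick up a switch to as-needed (PRN) prescribing

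*Protocol article*

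**What the plan says.** Two places define the primary outcome with a restriction to long-term medication. The Abstract has "proportion of residents receiving at least one antipsychotic prescription (long-term medication) after 12 months of follow-up", and the Trial objective section has "proportion of residents with at least one antipsychotic prescription (long-term medication) after 12 months of follow-up".

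Other places give it without the restriction. The Sample size calculation says "The primary endpoint of the study is the proportion of residents with at least one antipsychotic prescription after 12 months". The Statistical analysis section compares "the proportion of residents with at least one antipsychotic prescription after 12 months, proportions will be compared", and its secondary repeated-measures model of antipsychotic prescriptions at 3, 6, 9 and 12 months is also unrestricted. The Institutional level section records the proportion on an antipsychotic at baseline and 12 months, again unrestricted.

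The Trial objective section lists three secondary antipsychotic outcomes without a long-term limit: "Median daily dose of antipsychotics in chlorpromazine equivalents", "Proportion of residents with dementia with antipsychotic prescription", and the matching proportion among residents without dementia.

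The Resident level section gives the purpose of the medication data as "To analyse the proportion of residents receiving an antipsychotic prescription, the median daily dose of antipsychotic drugs in chlorpromazine equivalents" (and other psychotropic drugs). The data gathered for this at 3, 6, 9 and 12 months are "prescriptions of antipsychotics (long-term and pro re nata (PRN) medication) from routine documentation", with agent, dose and prescription period.

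**The concern.** The measure is narrower than the aim. Under the definition in the Abstract and Trial objective, a resident whose regular antipsychotic becomes a PRN-only order leaves the numerator and is counted as a success, although an antipsychotic prescription remains.

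The plan does watch for other forms of substitution: it lists outcomes for other psychotropic drugs and for physical restraints. The nearest substitute, the same drug on a PRN order, has no outcome stated to capture it.

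A shift could differ between arms. Only intervention homes have trained experts, whose duties include discussing medication reviews with colleagues or contacting the prescriber. Randomisation does not remove a shift that the intervention itself produces. If it occurred, a fall in long-term prescribing could be read as an equal fall in antipsychotic prescribing.

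The wording also supports two different primary endpoints, one without PRN and one with it.

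**Working it through.** **1. The plan's own figure.** Inputs from the Sample size calculation: 26% against 14% (a 12-point difference), two-sided alpha 0.05, power 90%, intra-class correlation 0.05, cluster size 65.

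- Per arm without clustering: n = [1.960·√(2·0.20·0.80) + 1.282·√(0.26·0.74 + 0.14·0.86)]² / 0.12² = 232, rounded up.
- Design effect: 1 + (65 − 1)·0.05 = 4.2.
- Clusters per arm: 232·4.2/65 = 974.4/65 = 14.99, so 15.
- Total: 30 + 6 = 36 clusters, and 36·65 = 2340 residents.

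The stated sample size reproduces. The present point is about what is counted and leaves this arithmetic alone.

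**2. The definitions side by side.**

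| Section | Long-term limit stated? | PRN mentioned? |
|---|---|---|
| Abstract; Trial objective (primary) | Yes | No |
| Trial objective (three secondary antipsychotic outcomes) | No | No |
| Institutional level | No | No |
| Resident level (data for proportion and dose) | No | Yes, collected with long-term |
| Sample size calculation; Statistical analysis | No | No |

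**3. Would the listed secondary outcomes show a switch?** They might, but they are not a dependable check.

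- Median dose: if taken over all residents, it is zero in both arms at 26% and 14% prevalence. If taken over users only, it loses switched residents when a user means a long-term user. The population is not stated. The number of PRN doses received is listed only among the medication-review data (baseline to 9 months), not among the 12-month outcome data.
- Proportions with and without dementia: either they follow the primary definition and leave PRN out, or they use a different one that is not stated. Neither is a single result for the whole sample.
- The repeated-measures model covers all observed residents but does not say whether PRN counts.

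**4. Size under assumed switching.** The Sample size calculation expects 30% at baseline, falling to 14% (intervention) and 26% (control). Stopped prescriptions are therefore 30 − 14 = 16 points and 30 − 26 = 4 points. Let c be the share of stopped prescriptions that become PRN-only, and assume that any other PRN-only use is equal in the two arms.

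- Same c in both arms: (26 + 4c) − (14 + 16c) = 12(1 − c).
- Conversion in the intervention arm only: 26 − (14 + 16c) = 12 − 16c.

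| c (assumed) | Equal conversion | Intervention arm only |
|---|---|---|
| 0% | 12 points | 12 points |
| 25% | 9 | 8 |
| 50% | 6 | 4 |
| 75% | 3 | 0 |

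In every row the long-term difference stays at 12 points.

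**5. Limiting case.** Suppose 26% in each arm have an antipsychotic of either kind, and a share of intervention-arm users is PRN-only. At 20% the apparent long-term difference is 0.26·20 = 5.2 points, and at 30% it is 0.26·30 = 7.8 points. With 15 clusters per arm (effective n = 15·65/4.2 = 232), the chance of a significant primary result is about 26% and 53%, with no difference in any-antipsychotic use.

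**The case against.** The best answer is that PRN may already be covered. Only the primary outcome carries the long-term limit, and the Resident level section ties PRN data to the proportion and dose analyses. This stands. A reader might infer that no listed outcome counts PRN, or that nothing listed could reveal a switch. The text does not support that: it leaves PRN open in the secondary outcomes and the repeated-measures model, and does not exclude it.

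Second, the operational definitions may be in Additional file 2, which is not shown. That is a fair answer for the secondary outcomes. It does not remove the mismatch over the primary endpoint, which lies within the article.

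Third, a long-term definition is a deliberate choice and fits the stated problem of antipsychotics given too long without review. A PRN order may also never be given, so counting it as equal to daily treatment can hide a real fall in exposure. Both points stand. They argue for keeping the long-term primary outcome and against making a claim depend on agreement of the two measures.

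Fourth, switching is conjecture. Both arms receive physician education and quarterly medication review by blinded specialists, who are shown the PRN antipsychotic details. This too stands: the documents make an arm-specific shift plausible but do not show one.

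**Conclusion.** The point holds in a limited form. As defined in the Abstract and Trial objective, the primary outcome counts a move to PRN-only prescribing as a reduction, which is narrower than the stated aim. The other sections do not keep to that definition. No secondary antipsychotic outcome is stated to include PRN, and none for the whole sample is named as any antipsychotic or as PRN only.

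A reader might go further and conclude that the primary result will overstate the effect by a known amount. It cannot be sized from the documents, which give neither a PRN rate nor a switching rate. The 9 or 8 points (25%) and 6 or 4 points (50%) are illustrations that rest on an assumed c and on the planned 30%, 26% and 14%. They concern prescriptions, not doses taken.

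The change is worth making because it decides whether a positive result can be read as less antipsychotic prescribing or only as less long-term prescribing.

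**What to change.** - Use one primary definition, long-term medication, in the Abstract, Trial objective, Institutional level, Resident level, Sample size calculation and Statistical analysis sections.
- For each secondary antipsychotic outcome, and for the repeated-measures model, state whether PRN counts.
- Add two secondary outcomes at 12 months: the proportion with any antipsychotic prescription (long-term or PRN) and the proportion with PRN only. Analyse both in the same set of residents and with the same cluster-adjusted method as the primary outcome.
- Word the primary conclusion as a reduction in long-term prescriptions, and report it beside the any-antipsychotic result.

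The added outcomes should be supportive and not a co-primary condition. The any-prescription measure has a known weakness: it can understate a real fall in exposure where PRN orders go unused.

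The cost is wording in the protocol and analysis plan and two further analyses. PRN prescriptions are already collected at 12 months, so no added visits or data items are needed, and the sample size is unchanged.

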### Participants and recruitment

#### Inclusion and exclusion criteria

The study will be performed in 36 nursing homes in the cities/catchment areas of Halle (Saale), Lübeck, and Witten. Individual nursing homes or units working independently within a large nursing home will be defined as a cluster.

Inclusion criteria will be nursing homes with at least 50 residents; each participating institution must have sufficient resources (staff, time) to conduct the study, and no special “dementia projects” or other activities potentially influencing the intervention will be allowed.

All residents within a cluster will be eligible to participate in the study. Exclusion criteria at the individual level will be:Temporary stay in respite care and/orPrimary diagnosis of schizophrenia, or bipolar disorder.

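### A median is a poor summary of antipsychotic dose here: it is zero in both arms over all residents, and over current users it compares groups selected by the intervention

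*Protocol article*

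**What the plan says.** The Trial objective section of the protocol article names "Median daily dose of antipsychotics in chlorpromazine equivalents" among the secondary outcomes at 12 months. The Resident level section repeats it as "the median daily dose of antipsychotic drugs in chlorpromazine equivalents" and says that it will be derived from routine records of long-term and as-needed prescriptions. Neither place says over which residents the median is taken.

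The trial is not restricted to antipsychotic users: "All residents within a cluster will be eligible to participate in the study", apart from two individual exclusions (respite stays; a primary diagnosis of schizophrenia or bipolar disorder). Under Sample size calculation, "the analyses will focus on the group of residents living in the nursing homes after 12 months"; residents who move in during the study may also join.

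The same section gives the expected rates. At the start, "we expect a baseline prevalence of antipsychotic prescription of 30" per cent; later, "we expect the prevalence in the control group to decline slightly to 26 % after 12 months"; and the trial is sized "to detect a 12 % difference in proportions from 26 % of the control group at 12 months with 90 % power", which puts the intervention arm at 14%.

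Under Statistical analysis, "For the secondary outcome measures, linear mixed models or generalised linear mixed methods will be used", with random effects for clusters. Secondary outcomes are exploratory, and details are referred to Additional file 2, which is not shown.

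**The concern.** Dose is a natural companion to the primary outcome, because a yes/no prescription endpoint cannot see a lower dose in a resident who stays on the drug. The summary chosen for it serves that purpose badly.

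- Over all residents, most doses are zero, so the median sits at zero whatever happens to the doses of those treated.
- Over current users at 12 months, membership of the group is itself an outcome of the intervention. Users left in the intervention arm need not resemble users in the control arm, and randomisation does not protect the comparison.
- The stated models work on means or on a link-function scale, so the reported effect would not be a difference in medians.

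At stake is a secondary result that either carries no information or shows a difference, in either direction, that cannot be read as a dose change.

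**Working it through.** **Inputs from the Sample size calculation:** 26% (control) and 26 − 12 = 14% (intervention) on an antipsychotic at 12 months; 30% at baseline; intra-class correlation 0.05; 65 residents per home; 15 homes per arm; two-sided 5% level; 90% power.

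**1. Reproducing the plan's figure.** Two proportions of 0.26 and 0.14 need 232 residents per arm without clustering. Design effect = 1 + (65 − 1) × 0.05 = 4.2. Homes per arm = 232 × 4.2 / 65 = 14.99, so 15. With six spare homes, (15 + 15 + 6) × 65 = 2340. Both figures agree with the article, so 26% and 14% are the rates it was planned on.

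**2. Median over all residents.** It exceeds zero only if at least half are on a drug. At the planning rates, 74% and 86% are at zero. The cluster-adjusted standard deviation of an arm's prevalence is √(p(1 − p) × 4.2 / 975), with 975 = 15 × 65:

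- control: √(0.26 × 0.74 × 4.2 / 975) = 0.029; (0.50 − 0.26) / 0.0288 = 8.3 standard deviations from one half
- intervention: √(0.14 × 0.86 × 4.2 / 975) = 0.023; (0.50 − 0.14) / 0.0228 = 15.8

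The expected median is also zero at the 30% baseline rate and at the 42.1% that the Background section gives for control homes in the UK trial. As-needed prescriptions would have to add 24 points in control and 36 in intervention to change this.

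**3. Median over current users.** The documents give no dose distribution and no link between dose and stopping, so what follows is illustrative. Assume log-normal user doses with log-SD s of 0.5 to 1.0, and that the intervention arm keeps r = 14/26 = 0.54 of the users that control has, with **no dose change** in those who continue.

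- If only the lowest doses stop, the remaining median is the 1 − r/2 = 0.731 quantile of the control distribution. Ratio to control = exp(0.615 s).
- If only the highest doses stop, it is the r/2 = 0.269 quantile. Ratio = exp(−0.615 s).
- If stopping is unrelated to dose, the ratio is 1.

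The ratio of mean dose per resident, zeros included, is Φ(s + 0.097) in the first case, Φ(0.097 − s) in the second and r in the third.

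| Who stops | User-median ratio, s = 0.5 / 0.8 / 1.0 | Mean-per-resident ratio, same s |
|---|---|---|
| lowest doses | 1.36 / 1.64 / 1.85 | 0.72 / 0.82 / 0.86 |
| unrelated to dose | 1.00 | 0.54 |
| highest doses | 0.74 / 0.61 / 0.54 | 0.34 / 0.24 / 0.18 |

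The first and last rows are extremes; partial dependence gives values in between. If continuing users also have their dose cut by a true 20%, every entry is multiplied by 0.8. The user-median ratio is then 0.80 when stopping is unrelated to dose, but still 1.09 to 1.48 when the lowest doses stop. The mean per resident falls in every row.

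**4. Outcome against model.** A linear mixed model compares means. If log doses were symmetric and modelled among users, it would also give a ratio of medians, but that is the comparison in step 3, and zeros cannot be logged.

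**5. A third population.** Take residents on an antipsychotic at baseline and count stopped doses as zero. Ignoring losses, at most 26/30 = 87% of them are still treated in control and at most 14/30 = 47% in intervention. The control median can then be above zero while the intervention median is zero.

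**The case against.** **The population may be fixed in Additional file 2.** This is fair, and the missing denominator is not the point made here. The article does commit to a median, and naming either of the two obvious populations would not repair it.

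**A reader might infer that the outcome cannot show a dose reduction at all.** The documents do not support that. Step 5 gives a population fixed before allocation whose median can differ between arms. A user-only median does move with a true dose cut; the trouble is attribution. A mixed model on all-resident doses would compare means and could detect a fall, in which case the fault is largely that the outcome is labelled a median. Against this, the article points its analyses at residents present at 12 months, and nothing shown indicates the baseline-user population.

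**A reader might also infer that remaining users in the intervention arm are on higher doses, so that the bias has a known sign.** Nothing in the documents says so. Step 3 goes both ways, and is zero if stopping is unrelated to dose. Users at 12 months also include later admissions and possibly new starters, so thinning 26% to 14% by stopping alone simplifies the design.

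**The outcome is exploratory, and a user dose read beside prevalence is ordinary description.** That stands, and it limits the importance of the point.

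**Conclusion.** The point holds as a poor choice of summary. That the all-resident median is zero in both arms follows from the article's own rates with a wide margin and needs no outside assumption. That a current-user median compares groups selected after randomisation follows from the design; only its size and direction depend on assumption, and the range shown (0.54 to 1.85 with no dose change) rests on log-normal doses and extreme stopping patterns. The mismatch with the stated models is evident from the text. The consequence is confined to one exploratory secondary outcome: the primary comparison and the sample size stand.

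**What to change.** - Define the outcome as mean daily chlorpromazine-equivalent dose per resident at 12 months, zero for non-users. Compare arms with the home as cluster, using robust or bootstrap intervals or a two-part model (any use; dose if used).
- As a supporting analysis, report the 12-month dose, zeros included, among residents on an antipsychotic at t0, adjusted for t0 dose. State that about 25% are expected to be lost to death or moving, so this group too is exposed to selection.
- Do not adjust for the so-called baseline dose of residents admitted later. It is recorded at the next measurement point after admission, hence after randomisation, and may already reflect the intervention.
- Report the median among current users as description only.

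The cost is wording in the analysis plan, since the dose data are already to be collected. The price is a summary that is sensitive to a few high doses and driven largely by the change in prevalence, which is why the two-part model or the baseline-user analysis should be read beside it.
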